## Abstract

**Introduction::**

While the role of inflammation in acute coronary events is well established, the impact of inflammatory-mediated vulnerability of coronary plaques from the entire coronary tree, on the extension of ventricular remodeling and scaring, has not been clarified yet.

**Materials and methods::**

The present manuscript describes the procedures of the VIABILITY trial, a descriptive prospective single-center cohort study. The main purpose of this trial is to assess the link between systemic inflammation, pan-coronary plaque vulnerability (referring to the plaque vulnerability within the entire coronary tree), myocardial viability and ventricular remodeling in patients who had suffered a recent ST-segment elevation acute myocardial infarction (STEMI). One hundred patients with STEMI who underwent successful revascularization of the culprit lesion in the first 12 hours after the onset of symptoms will be enrolled in the study. The level of systemic inflammation will be evaluated based on the serum biomarker levels (hs-CRP, matrix metalloproteinases, interleukin-6) in the acute phase of the myocardial infarction (MI) and at 1 month. Pan-coronary plaque vulnerability will be assessed based on serum biomarkers known to be associated with increased plaque vulnerability (V-CAM or I-CAM) and at 1 month after infarction, based on computed tomographic angiography analysis of vulnerability features of all coronary plaques. Myocardial viability and remodeling will be assessed based on 3D speckle tracking echocardiography associated with dobutamine infusion and LGE-CMR associated with post-processing imaging methods. The study population will be categorized in 2 subgroups: subgroup 1 - subjects with STEMI and increased inflammatory response at 7 days after the acute event (hs-CRP ≥ 3 mg/dl), and subgroup 2 - subjects with STEMI and no increased inflammatory response at 7 days (hs-CRP < 3 mg/dl). Study outcomes will consist in the rate of post-infarction heart failure development and the major adverse events (MACE) rate.

**Conclusion::**

VIABILITY is the first prospective study designed to evaluate the influence of infarct-related inflammatory response on several major determinants of post-infarction outcomes, such as coronary plaque vulnerability, myocardial viability, and ventricular remodeling.

## Introduction

1

### Background and rationale

1.1

It is well-known that the highest risk of death following an acute myocardial infarction (AMI) is within the first hours from onset. In the latest years, introduction of coronary care units and large-scale implementation of networks for emergency myocardial revascularization, as well as development of reperfusion and pharmacological therapies, led to a significant decrease in mortality rates following AMI. However, the high incidence of post-infarction heart failure is still affecting the long-term outcomes of these patients.^[1–4]^

Congestive heart failure (CHF) as a long-term complication following AMI, although having a relatively low incidence in the primary percutaneous coronary intervention (PCI) era, is an important predictor of mortality and morbidity, at the same time leading to increased health-care costs and decreased quality of life.^[5]^ Predictors for CHF following an AMI include preexistent heart failure, traditional cardiovascular risk factors (diabetes, hypertension, old age, smoking, chronic renal disease), previous myocardial infarction (MI) with or without revascularization, rhythm disturbances during the acute phase of the coronary event, delayed revascularization times, multivessel coronary artery disease (CAD), enhanced inflammatory response, or no-reflow phenomenon after revascularization.^[6–9]^

Multiple coinciding pathophysiological mechanisms may lead to heart failure after AMI, both during the index event and later on. These include myocardial necrosis and stunning, inflammation, reperfusion injury, microvascular obstruction, fibrosis and remodeling. CHF during the acute phase of an acute coronary syndrome results from a combination of myocardial necrosis and stunning, as well as ischemic (including papillary muscle dysfunction and subsequent mitral regurgitation, cardiac tamponade, ventricular overload) and arrhythmic complications. Later onset of CHF arises as a consequence of myocardial scarring and remodeling.^[5,10–12]^

The major aim of the urgent revascularization in ST-elevation myocardial infarction (STEMI) is to save myocardial tissue from death and necrosis, in order to recover viable myocardium. Despite a timely revascularization of the epicardial culprit coronary artery, a significant proportion of patients do not present the typical signs for a successful reperfusion, this being defined as the no-reflow phenomenon. Various mechanisms have been incriminated in an attempt to provide an explanation for this phenomenon, including microvascular embolization, endothelial dysfunction due to an exaggerated inflammatory response, or reperfusion injury. The consequences of this phenomenon are expansion of the infarct size, life-threatening arrhythmias, early development of CHF, and enhanced ventricular remodeling and dilation. Diagnosis of no-reflow can be achieved in the catheterization laboratory, during the revascularization procedure, or via imaging techniques such as gadolinium contrast magnetic resonance, contrast echocardiography or nuclear imaging.^[13–16]^

It is well-known that one of the major factors that trigger an AMI is the systemic inflammation, which has a direct influence on coronary plaque vulnerability.^[17]^ Atheromatous plaques develop and progress due to a chronic non-resolving inflammatory process that occurs at the site of an endothelial injury caused by turbulent blood flow. The atherosclerotic lesions can evolve in a silent manner for a number of years without causing an acute event.^[18]^ However, some plaques become unstable by acquiring several phenotypic changes (large necrotic core, thin cap fibroatheroma, microcalcifications, vascular remodeling) which make them prone to rupture.^[19,20]^ Several studies have shown that vulnerable plaques are associated with an enhanced inflammatory response, which causes overexpression of the vulnerability features, with consequent rupture and thrombosis.^[20–22]^ Furthermore, myocardial injury triggers an inflammatory cascade, which is persistent during the first 3 to 5 days following the acute event, having a benefic reparatory effect.^[23]^ The persistence of an elevated systemic inflammation after AMI after day 3 to 5 has deleterious effects, stimulating the process of left ventricular remodeling and evolution towards CHF. Moreover, the enhanced inflammation secondary to myocardial ischemia, may lead to vulnerabilization of additional atherosclerotic plaques thorough the vascular system, which might explain increased rates of acute coronary and cerebrovascular events in patients that have already suffered an AMI.^[8,24,25]^

The exact influence of various pathophysiological mechanisms, such as no-reflow phenomenon or increased inflammatory response on a pan-coronary level, on the process of ventricular remodeling is not fully understood. Understanding the complex heterogenous interaction of these components could help to identify patients at a higher risk for developing heart failure, as well as subsequent coronary and cerebrovascular events, after they have already suffered an AMI.

The present manuscript describes the procedures of the VIABILITY trial, a descriptive prospective single-center cohort study which intends the assessment of the link between systemic inflammation, pan-coronary plaque vulnerability (referring to the plaque vulnerability within the entire coronary tree), myocardial viability and ventricular remodeling in patients who had suffered a recent STEMI.

### Study objectives

1.2

The *primary objective* consists in the evaluation of the relationship between coronary inflammation-mediated plaque vulnerability, myocardial viability and ventricular remodeling in the post-infarction period.

The *secondary objectives* of the study are:

(1)to assess the effect of systemic inflammation on the structural remodeling process of the left ventricle (LV) following an AMI and(2)to evaluate the impact of local inflammatory response on pan-coronary plaque vulnerability in the post-infarction period.

## Methods/design

2

### Study design

2.1

VIABILITY is a prospective, non-randomized, cohort study, carried out in a single-center, which aims to assess the link between systemic inflammation, pan-coronary plaque vulnerability (referring to the plaque vulnerability within the entire coronary tree), myocardial viability and ventricular remodeling in patients with recent STEMI.

### Ethics approval

2.2

The VIABILITY clinical study is approved by the local Ethics Committee for Scientific Research of the University of Medicine and Pharmacy of Tirgu-Mures, Romania (certificate of approval: 349/13.12.2017) and the Ethics Committee for Scientific Research of the Cardio Med Medical Center Tirgu Mures, Romania (certificate of approval: 30/28.12.2017). All study procedures will be conducted according to the *Declaration of Helsinki*. Each subject will provide sign written informed consent before randomization process.

### Study population

2.3

VIABILITY will be a single-center, observational, non-randomized study including 100 patients with STEMI who underwent successful revascularization of the culprit lesion in the first 12 hours after the onset of symptoms.

#### Inclusion criteria

2.3.1

Patients with STEMI treated by primary PCI within the first 12 hours after the onset of symptoms;Body mass index (BMI) under 40 kg/m^2^;Signed written informed consent;Subject at age of majority.

#### Exclusion criteria

2.3.2

Documented ACS within last month before randomization;Patient disapproval to provide written informed consent;Intolerance to iodine contrast agent;Conditions associated with contraindication for CMR examination;Women during pregnancy or lactation period;Women able to procreate without any contraceptive usage;Chronic kidney disease (glomerular filtration rate <60 ml/min/1.73 m^2^) or acute renal injury that requires hemodialysis;Any type of neoplasia documented in the last 3 years before randomization;Expectation of life <1 year.

### Study settings

2.4

The VIABILITY study will be carried out in the Center of Advanced Research in Multimodality Cardiac Imaging of the Cardio Med Medical Center and in the Clinic of Cardiology of the County Clinical Emergency Hospital Tirgu Mures, affiliated to the University of Medicine, Pharmacy, Sciences and Technology of Tirgu Mures, Romania. Funding will be provided via research grant number UEFISCDI PN-III-P2–2.1 BG-2016–0343 – COROFLOW (contract 43/05.09.2016, full name: New technologies for 3D computational simulation of coronary circulation and myocardial perfusion based on fusion imaging), financed by the European Union and the Romanian Government through the Ministry of Education and Research, which was selected for funding in a national competition for research grants, following an international peer-review selection process.

### Study population and subgroups

2.5

This study will enroll 100 patients with STEMI meeting the inclusion criteria. Study subjects will be distributed in 2 groups: group 1 – patients with STEMI and increased inflammatory response at 7 days after the acute event (hs-CRP ≥ 3 mg/dl) and group 2 - subjects with STEMI and no increased inflammatory response at 7 days (hs-CRP <3 mg/dl).

### Study procedures and outcome assessment

2.6

Medical records, physical exam, laboratory analysis: complete blood count (CBC), biochemistry, levels of high sensitivity C-reactive protein (hs-CRP), MMPs, IL6, NT-pro-BNP, adhesion molecules;electrocardiogram (ECG);TTE with morphological measurements, assessment left ventricular systolic and diastolic performance, speckle tracking echo, Dobutamine viability test;LGE-CMR with the evaluation of myocardial scar and fibrosis, ventricular function and remodeling index;Angiographic Computed Tomography (Angio-CT) with assessment of coronary plaque vulnerability (based on vulnerability features: positive remodeling, spotty calcification, napkin-ring sign, low-density plaque) and myocardial perfusion.

#### Biomarkers assays

2.6.1

Routine biochemistry and CBC analysis will be performed at the main laboratory of the Emergency Clinical County Hospital of Tirgu-Mures, immediately after randomization. Inflammatory status (hs-CRP levels) will be evaluated at 7 days after the acute cardiac event via immunoturbidimetric assay. Adhesion molecules (VCAM, ICAM), matrix metalloproteinase 9, and interleukin-6 serum levels will be evaluated using enzyme linked immunosorbent assay. Serum inflammatory biomarkers will be analyzed in Advanced Medical and Pharmaceutical Research Center of the University of Medicine and Pharmacy Tirgu-Mures, Romania. N-terminal prohormone of brain natriuretic peptide (NT-proBNP) levels will be evaluated at randomization and at the last follow-up visit, at the main laboratory of the Emergency Clinical County Hospital of Tirgu-Mures by electrogenerated chemiluminescence.

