#### Study procedures

2.9.6

Medical records, physical exam, laboratory analysis (CBC, biochemistry, serum levels of hs-CRP, MMPs, IL6, NT-pro-BNP, adhesion molecules);ECG.TTE with morphological measurements, assessment left ventricular systolic and diastolic performance, speckle tracking echo, Dobutamine viability test.LGE-CMR with the evaluation of myocardial scar and fibrosis, ventricular function and remodeling index.Angio-CT with assessment of coronary plaque vulnerability (based on vulnerability features: positive remodeling, spotty calcification, napkin-ring sign, low-density plaque) and myocardial perfusion.

All study procedures are illustrated in Figure 1, which presents the VIABILITY flowchart.

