## Discussions

3

This manuscript presents the protocol of a clinical study, conducted in a single center, with the purpose to analyze the link between systemic inflammation, pan-coronary plaque vulnerability, myocardial viability and remodeling in patients who had suffered a recent STEMI.

It is well-known that one of the major factors that trigger an AMI is the systemic inflammation, which has a direct influence on coronary plaque vulnerability, usually related to decreased structural stability.^[26]^ According to histological studies, prone-to-rupture plaques present significant differences as compared with stable obstructive coronary plaques.^[27]^ Those high-risk plaque features associated with the presence of acute coronary syndrome (ACS) have been defined by a series of Angio-CT studies and include larger plaque volume, plaque with low attenuation, positive remodeling, large plaque burden, spotty calcium, and napkin-ring sign. Ruptured plaques, the main cause of MIs, proved to have fibrous caps that contain elevated levels of proteases, including metalloproteinases (MMPs). Histologic studies provide strong associative evidence that MMPs promote plaque vulnerability in humans.^[28]^ Similarly, two overexpression studies give a clear evidence of plaque disruption in the presence of high MMP-9 levels, that are thought to influence the rates of atherogenesis and the stability of atherosclerotic plaques.^[29,30]^

Therefore, one of the study objectives will be to investigate the impact of local inflammatory response, assessed by inflammatory biomarkers and adhesion molecules, on pan-coronary plaque vulnerability based on vulnerability features determined via coronary CT angiography, following an AMI.

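### MMP-9 is specified in serum, where release from blood cells during clotting may inflate it and confound it with leukocyte count

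*Protocol article*

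**What the plan says.** Section 2.6.1 (Biomarkers assays) names both the matrix and the method: "Adhesion molecules (VCAM, ICAM), matrix metalloproteinase 9, and interleukin-6 serum levels will be evaluated using enzyme linked immunosorbent assay". Two other places confirm that serum covers the metalloproteinases and not only interleukin-6. The Abstract says "The level of systemic inflammation will be evaluated based on the serum biomarker levels (hs-CRP, matrix metalloproteinases, interleukin-6", with measurement in the acute phase and at 1 month. The procedures list in section 2.9.6 has "serum levels of hs-CRP, MMPs, IL6, NT-pro-BNP, adhesion molecules".

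MMP-9 bears on the secondary objectives by two routes. As one of three named measures of systemic inflammation, it bears on the first, about systemic inflammation and left ventricular remodeling. The second, in section 1.2, is "to evaluate the impact of local inflammatory response on pan-coronary plaque vulnerability in the post-infarction period", and section 3 says how the exposure is measured: "the impact of local inflammatory response, assessed by inflammatory biomarkers and adhesion molecules, on pan-coronary plaque vulnerability". Section 3 also gives the reason for interest in MMP-9, citing "clear evidence of plaque disruption in the presence of high MMP-9 levels".

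**The concern.** The rationale treats MMP-9 as a protease acting in the plaque, so the quantity of interest is MMP-9 present in the patient. A serum tube contains that amount plus whatever blood cells release while the sample clots, and an immunoassay for the protein does not separate the two. The released part depends on how many leukocytes are in the tube.

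In this population that dependence matters. The day 0 sample is drawn during a STEMI, when the infarct raises the leukocyte count. Two errors are possible:

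- **Dilution.** Release unrelated to the outcome adds noise and weakens a true association.
- **Distortion.** Release that follows leukocyte count, and through it infarct severity, can produce an association with scar or remodeling that does not come from circulating MMP-9.

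What is at stake is the interpretation of MMP-9 in the secondary objectives.

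**Working it through.** **Step 1: is the matrix stated or merely omitted?** It is stated, in three consistent places (Abstract, 2.6.1, 2.9.6). A laboratory manual could add clotting and centrifugation times, but it could not change serum to plasma without contradicting this text. The absence of handling times from a journal article is not part of the point.

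**Step 2: what depends on MMP-9?**

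| Element | Basis in the article | Uses MMP-9? |
|---|---|---|
| Grouping (2.5) | hs-CRP at day 7 | No |
| Primary outcome (2.8) | Heart failure readmission or ejection fraction | No |
| Secondary outcomes (2.8) | Clinical events | No |
| Sample size (2.10) | Major adverse event rates | No |
| Secondary objectives (1.2, with Abstract and section 3) | Inflammatory biomarkers against remodeling and plaque features | Yes, as one of several markers |

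**Step 3: how large could the effect be?** The plan has no figure to reproduce. Everything below is illustration on assumed inputs.

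Assumptions: circulating MMP-9 is log-normal with log SD 0.5. Release in the tube equals (ratio − 1) times a log-normal factor with log SD 0.4 to 0.6. Serum is the sum of the two, and the ratio is the assumed serum-to-plasma ratio. Let c be the simulated correlation of log serum with log circulating MMP-9. If the outcome is related to serum only through circulating MMP-9, the observed correlation is the true correlation times c. Power for N = 100, two-sided 5%, by Fisher's z is Φ(atanh(r) × √97 − 1.96).

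Without release, r = 0.30: atanh(0.30) × √97 = 0.3095 × 9.849 = 3.048, and Φ(3.048 − 1.96) = 86%.

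| Ratio | c, release independent | Observed r | Power | c, release correlated 0.5 with circulating | Power |
|---|---|---|---|---|---|
| 1.5 | 0.82–0.91 | 0.25–0.27 | 69–79% | not needed | – |
| 2 | 0.62–0.77 | 0.19–0.23 | 46–63% | 0.83–0.89 | 71–77% |
| 3 | 0.40–0.54 | 0.12–0.16 | 22–37% | 0.73–0.80 | 59–67% |

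Power is computed from unrounded c. Example at ratio 3, release log SD 0.4: c = 0.542, r = 0.30 × 0.542 = 0.163, atanh(r) × √97 = 1.616, and Φ(1.616 − 1.96) = 37%.

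**Step 4: a two-group comparison.** Section 2.11 names two-group tests and no correlation, so the same attenuation is shown on that scale. Take 50 per group and a standardised difference of 0.65, chosen because it gives 90% power: Φ(0.65 × √25 − 1.96) = Φ(1.29) = 90%. If a share s of serum variance is unrelated release, the difference shrinks by √(1 − s):

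- s = 0.25: 0.563, power 80%
- s = 0.50: 0.460, power 63%
- s = 0.75: 0.325, power 37%

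**Step 5: the distortion side.** Suppose release, through leukocyte count, correlates 0.40 with an outcome and circulating MMP-9 correlates zero. With independent release and ratio 2, log serum correlates 0.61–0.75 with release. Serum MMP-9 then shows r = 0.40 × 0.61 to 0.40 × 0.75, or 0.25 to 0.30, and is significant 69% to 86% of the time.

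**The case against.** A reader might infer that the serum result largely reflects white-cell count and clotting time and hardly measures circulating MMP-9. The documents do not support that. They give no serum-to-plasma ratio, and at an assumed ratio of 1.5 serum still correlates 0.82–0.91 with the circulating value. Independent release is also a harsh assumption, since the infarct can raise both leukocyte count and circulating MMP-9. With a correlation of 0.5 between them, power at ratio 3 is 59–67%, not 22–37%. This objection stands, and it limits the claim to possible inflation and confounding of unknown size.

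A second objection is that MMP-9 is peripheral. It is one of several markers, the Abstract's biomarker assessment of plaque vulnerability names the adhesion molecules and not MMP-9, and the MMP-9 text in section 3 is background from histology and overexpression studies. For a general marker of inflammation, some tracking of leukocyte burden does less harm than it would for a plaque-specific protease. This stands as a limit on scope. It does not remove the point, because the article names metalloproteinases as a measure of systemic inflammation and ties the second secondary objective to the inflammatory biomarkers.

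A third objection is that the mechanism comes from outside the documents. That is true: release during clotting is general laboratory knowledge, and the article neither mentions it nor gives a figure. It is enough to question the choice of matrix but not to put a size on the error.

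**Conclusion.** The point holds as a measurement-quality weakness in one secondary biomarker. Serum is an explicit choice, and serum MMP-9 may be inflated and confounded by leukocyte count. Associations of MMP-9 with plaque features and remodeling may be weakened or distorted as a result. The hs-CRP grouping, the primary and secondary outcomes and the sample size are unaffected.

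The size is unknown. In the illustration, power of 86% for a true correlation of 0.30 drops to 69–79% at ratio 1.5 and to 22–37% at ratio 3 with independent release, or 59–67% at ratio 3 when release and circulating MMP-9 correlate 0.5. These figures depend on the assumed ratio, log SDs and dependence, and on a correlation analysis that section 2.11 does not list. They show that the matrix could matter, not how much it does.

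**What to change.** In section 2.6.1, specify MMP-9 in anticoagulated plasma (for example citrate) from the same blood draws, centrifuged promptly. Keep serum for VCAM, ICAM and IL-6. Change the Abstract and section 2.9.6 so that serum no longer covers the metalloproteinases. The Abstract plans biomarkers at 1 month but the Visit 2 list (2.9.3) shows no blood sample, so the plasma tube should be written into that visit too.

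Where only serum exists, do not interpret it as circulating MMP-9. Adjustment for a same-visit white-cell count can be reported as a sensitivity analysis only. The count is itself part of the inflammatory response, so adjusting may remove true signal. The day 0 blood count (2.9.1) cannot correct a 1-month sample, and Visit 2 lists no blood count.

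Cost: one extra tube at each draw and a line in the laboratory instructions. The downside is that plasma values are not comparable with serum already stored, so the two should not be pooled.
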